### Endpoints

The primary endpoint is the 3-year disease-specific survival (intention-to-treat). Secondary endpoints include:
Completion of chemotherapy,Completion of SBRT,Acute and late toxicities,Resection rate,Perioperative morbidity and mortality,Rate of margin-free surgery,Progression-free survival (local/distant progression), intention-to-treat,Recurrence-free survival in the subset of patients undergoing resection (per-protocol),3-year disease-specific survival in the subset of patients undergoing resection (per-protocol).

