### Follow-up

#### Efficacy assessment

Patients will be followed for 36 months postoperatively or from the time of early progression/surgical ineligibility. Follow-up visits will take place every 3 months after surgery for the first 12 months, then on a 6-month basis up to study completion/death (Table 1). In patients with disease progression during the neoadjuvant phase and in those who were not eligible for surgical exploration, follow-up visits will be scheduled on a 6-month basis. The surveillance protocol includes a thin-slice contrast-enhanced, tri-phasic computed tomography, Ca 19.9 measurement and a thorough clinical examination. Complementary gadolinium-enhanced magnetic resonance and/or 18-FDG positron-emission tomography will be performed in selected cases, following multidisciplinary consultation. Disease recurrence (either local or distant) is defined as the presence of biopsy-proven tumor or was assumed based on the above-mentioned cross-sectional imaging studies, in conjunction with clinical picture and/or serum Ca 19.9 levels.

**Table 1 Tab1:** Flow-chart of study procedures

	Pre-study	PC completion	SBRT completion	Surgery + IORT^**a**^	Follow-up							
Assessments												
Informed consent	X				3 mo	6 mo	9 mo	12 mo	18 mo	24 mo	30 mo	36 mo
Physical evaluation	X	X	X	X	X	X	X	X	X	X	X	X
AE assessment		X	X	X	X	X	X	X	X	X	X	X
Ca 19–9, CEA	X	X	X	X	X	X	X	X	X	X	X	X
CT-scan (thorax/abdomen)	X	X	X		X	X		X	X	X	X	X
MRI	Optional	Optional	Optional									

*PC* primary chemotherapy, *IORT* intraoperative radiation therapy

^a^at the time of hospital discharge

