#### Survival analysis

The progression-free survival (for patients who will not ultimately receive pancreatectomy due to unexpected locally unresectable or metastatic disease) and the disease-specific survival (for patients receiving pancreatectomy) will be calculated from both the date of diagnosis and the date of last follow-up or recurrence/death from disease, using the Kaplan-Meier method. Pairwise differences in survival will be assessed using the log-rank test. The analysis of recurrence and survival predictors will be carried out using the proportional hazard Cox regression (backward stepwise elimination technique, Wald method, *P* < .05 for entry, *P* > .10 for removal). Statistical significance will be determined by a 2-sided *P* value less than .05. Data will be using SPSS software (IBM).

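### PFS and disease-specific survival share one end-date clause: read literally it ends disease-specific survival at recurrence, and on every reading it leaves at least the non-disease deaths out of PFS

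*Protocol article*

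**What the plan says.** The Survival analysis section names two endpoints in one sentence. The first is "The progression-free survival (for patients who will not ultimately receive pancreatectomy due to unexpected locally unresectable or metastatic disease"; the second is "the disease-specific survival (for patients receiving pancreatectomy) will be calculated from both the date of diagnosis". Both then run to the same end: "the date of last follow-up or recurrence/death from disease, using the Kaplan-Meier method". Nothing in the sentence assigns recurrence to one endpoint and disease death to the other.

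The Endpoints section is brief. On the primary endpoint it says "The primary endpoint is the 3-year disease-specific survival (intention-to-treat". PFS appears as "Progression-free survival (local/distant progression), intention-to-treat", with no mention of death. For resected patients, RFS and DSS are listed as two separate items: "Recurrence-free survival in the subset of patients undergoing resection (per-protocol),3-year disease-specific survival in the subset of patients undergoing resection (per-protocol".

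Efficacy assessment defines recurrence by tissue or imaging, again without death: "Disease recurrence (either local or distant) is defined as the presence of biopsy-proven tumor or was assumed based on the above-mentioned cross-sectional imaging studies".

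**The concern.** A time-to-event endpoint is fixed by its event. Here one clause sets the event for two endpoints that should have different events, so the reported figures depend on how an analyst reads a slash.

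Two things are at stake. If recurrence ends DSS, a patient whose disease returns but who is still alive at three years counts as a disease-specific death. If PFS does not count all deaths, a patient who dies without documented progression is treated as progression-free up to the point of censoring, and the PFS curve is too high. The first matters because the primary endpoint is a 3-year DSS and the article gives no other event rule for DSS. The second concerns a secondary endpoint only.

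This is not a detail left to an analysis plan that is not shown. The article states an event rule, and the rule does not fit both endpoints.

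**Working it through.** No figure in the article depends on this clause, so there is nothing to reproduce. The check is to list the possible readings and compare each with the Endpoints section. Recurrence is taken to cover progression, as it must for patients who are never resected.

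| Reading | DSS event | PFS event | Result |
|---|---|---|---|
| A. Literal: either event ends both | recurrence or disease death | recurrence or disease death | DSS becomes a recurrence-free measure; PFS censors non-disease deaths |
| B. Distributive: one event each | disease death | recurrence | DSS correct; PFS counts no deaths and is a time to progression |
| C. Mixed | disease death | recurrence or disease death | DSS correct; PFS censors non-disease deaths |

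**Reading A, an invented example.** A resected patient recurs at month 14 and is alive at month 40. At 36 months this patient is alive, so DSS should show no event. The literal rule records an event at month 14. The separate listing of RFS and DSS in resected patients then has no purpose.

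**Do non-disease deaths arise and get recorded?** Yes. Postoperative management records deaths within 90 days of surgery, and Expected adverse event reporting requires every death to be reported whatever its cause. The article gives no expected number of either.

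**Illustration for PFS, under assumptions.** Background reports a median PFS of 14.7 months for all eligible patients in a single-arm phase 2 trial of borderline resectable disease. Assume exponential times, and assume that a share s of PFS events are deaths that the rule censors. These shares are not in the documents.

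- Hazard: ln 2 / 14.7 = 0.0472 per month.
- 3-year PFS with every death counted: exp(−0.0472 × 36) = 18.3%.
- 3-year PFS with share s censored: exp(−0.0472 × (1 − s) × 36), which is 19.9% for s = 5% and 25.7% for s = 20%.
- Median: 14.7 / (1 − s), which is 15.5 months for s = 5% and 18.4 months for s = 20%.

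This shows the direction and how the error grows with s. It does not estimate the error in this trial.

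**The case against.** The strongest defence is that the intended meaning can be recovered. The name DSS states its own event, and since RFS is listed beside it for the same patients, few analysts would end DSS at recurrence. Reading B also agrees with the Endpoints section, whose gloss on PFS mentions only progression. On that view the case against PFS rests on the usual meaning of the term, not on a contradiction between sections.

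Much of this stands. Reading A is the least likely in practice, and Reading B is internally consistent. But the analyst would have to set aside the printed rule to avoid A. And an endpoint called progression-free survival that does not treat every death as an event is misnamed under B and C alike.

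A reader might go further and infer any of three stronger points, none of which the article supports.

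- **That every reading either ends DSS at recurrence or makes PFS ignore all deaths.** Reading C does neither.
- **That the literal rule costs DSS about 33 points at three years.** Exponential curves through the all-eligible medians in Background give 0.5^(36/14.7) = 18.3% for PFS and 0.5^(36/37.7) = 51.6% for overall survival. But Survival analysis applies DSS to resected patients. For resected patients the same trial had a median PFS of 48.6 months, which by the same formula gives 0.5^(36/48.6) = about 60%, and its median overall survival was not reached. No gap for resected patients can be computed.
- **That a large share of patients would die unseen between 6-monthly scans and be censored in PFS.** Efficacy assessment assigns 6-monthly visits to patients who progressed during neoadjuvant treatment, who already have their PFS event, and to those not eligible for exploration. Visits after surgery are 3-monthly in the first year, with CT at 3, 6 and 12 months in Table 1. Moreover, disease deaths are counted under A and C.

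**Conclusion.** The clause is wrong as written. Its literal reading turns DSS into a recurrence-free measure; its two other readings leave DSS intact. On every reading PFS is overstated, because at least the deaths not attributed to disease are censored, and under the distributive reading all deaths are. This conclusion takes PFS in its usual sense of alive without progression, and assumes that at least one patient dies without prior progression from a cause the rule does not count.

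The documents do not allow the size to be estimated. The PFS illustration rests on exponential times and assumed shares, and the conclusion does not need it. Nor does the article show that the primary result will be miscalculated: that follows only if the literal reading is applied to the primary DSS.

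**What to change.** Replace the shared clause in Survival analysis with one event per endpoint:

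- **PFS:** first documented progression or recurrence, or death from any cause.
- **RFS (resected patients):** first recurrence, or death from any cause.
- **DSS:** death from pancreatic cancer only, with follow-up continuing past recurrence.

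Make the change before any analysis, so that the choice cannot depend on the results. The cost is a short rewording. Recurrence and death are already collected, and visits are already planned up to death or study completion, so no new data are needed. The downside is that reported PFS becomes slightly less favourable than under the present clause.

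Which patients each endpoint covers is a separate matter. Survival analysis limits PFS to unresected and DSS to resected patients, whereas Endpoints calls PFS and the primary DSS intention-to-treat. The same rewording is a convenient place to reconcile the two sections.

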### Statistical considerations

#### Sample size calculation

The estimate of accrual was calculated hypothesizing that total neoadjuvant therapy with FOLFIRINOX + SBRT + IORT will improve the 3-year survival rate up to 37% in comparison with cohort-level institutional data (patients < 75 years with BRPC undergoing neoadjuvant FOLFIRINOX, 3-year survival of 23.7%) Accrual time was set at 36 months and follow-up at 36 months. At a power of 0.90, and alpha of 0.5 a sample size of 100 patients was calculated assuming a non-parametric estimate of survival distribution. The SWOG Cancer Research and Biostatistics one-arm trial with time-to-event data sample size calculator was employed [26].

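### Backward stepwise Cox selection makes the reported intervals for predictors too narrow and the retained hazard ratios too large

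*Protocol article*

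**What the plan says.** The Survival analysis section states: "The analysis of recurrence and survival predictors will be carried out using the proportional hazard Cox regression". The method is given as "backward stepwise elimination technique, Wald method", with an entry threshold of .05 and a removal threshold of .10. The same paragraph adds: "Statistical significance will be determined by a 2-sided *P* value less than .05". It states no shrinkage, validation, multiplicity adjustment or exploratory label for the predictor results.

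Under Sample size calculation, "a sample size of 100 patients was calculated" for 3-year survival of 37% against 23.7%. The Endpoints section does not list the predictor analysis.

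**The concern.** The rule keeps a term because its estimate is large relative to its standard error in these data. It then reports that same estimate, standard error and P value as if the term had been chosen beforehand. Retained hazard ratios are therefore pushed away from 1, and their nominal 95% intervals miss the truth too often. The effect grows as events become fewer, so the resected subset suffers most.

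What is at stake is the credibility of the published hazard ratios and intervals for predictors. The selection rule is stated in the text, so this is not a matter of detail left to a fuller document.

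**Working it through.** **The plan's figure.** The article gives no event count or error rate for the predictor analysis, so N = 100 is the only figure to reproduce. A one-sample binomial approximation at one-sided alpha 0.05 and power 0.90 gives [1.645 × √(0.237 × 0.763) + 1.282 × √(0.37 × 0.63)]² / 0.133² = 98.2, close to 100. The alpha printed in that section (0.5) does not give 100. That is a separate matter, and N = 100 is taken as given here.

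**Deaths by 3 years, from the document's rates.**
- All patients: 100 × (1 − 0.37) = 63 under the target and 100 × (1 − 0.237) = 76 under the reference rate.
- Resected, low anchor: the Background cites 51% resected among patients under 75 on FOLFIRINOX and a median survival of 35.4 months after resection, so about half are dead at 3 years: 51 × 0.5 ≈ 25.
- Resected, high anchor: 88.9% in the institution's own series, 89 × 0.5 ≈ 45.

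**Hand approximation.** Assumptions: one standardised factor with true HR 1.3 (log 0.262), k − 1 null factors, and SE ≈ 1/√deaths.
- A null factor stays if P ≤ .10. Its 95% interval then includes HR 1 only if P > .05, so its coverage given retention is 1 − .05/.10 = 50%, whatever the sample size.
- The true factor stays with probability q = Φ(z − 1.645), where z = 0.262/SE. This gives q = 0.669 (63 deaths), 0.546 (45) and 0.370 (25). Its coverage once kept, c = [0.975 − Φ(1.645 − z)]/q, is 0.963, 0.954 and 0.932.
- Coverage over retained terms = [q·c + (k − 1) × 0.10 × 0.50] / [q + (k − 1) × 0.10]. With 63 deaths and k = 5: (0.644 + 0.200)/1.069 = 79%.
- Mean log HR once kept = 0.262 + SE × φ(1.645 − z)/q. With 63 deaths: 0.262 + 0.126 × 0.542 = 0.331, HR 1.39. With 45 deaths: HR 1.45. With 25 deaths: 0.262 + 0.200 × 1.02 = 0.466, HR 1.59.

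**Simulation.** Exponential survival, censoring at 36 months, half continuous and half binary factors, backward Wald elimination at P > .10. Coverage of nominal 95% intervals of retained terms:

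| Patients / deaths | By hand, k = 5 / 10 | Simulated, k = 5 / 10 |
|---|---|---|
| 100 / 63 | 79% / 70% | 75% / 62% |
| 89 / 45 | 76% / 67% | 73% / 60% |
| 51 / 25 | 71% / 63% | 65% / 50% |

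The full model without selection covers 92-95%. The HR of 1.3 is reported, when retained, as about 1.4-1.5 (89-100 patients) and 1.65-1.7 (about 50), against 1.32-1.40 in the full model. Repeat runs agree to within about 3 points. The lowest full-model coverage seen in any run was 90% (50 patients, 10 factors). Simulated coverage lies below the hand values, as expected when Wald tests run somewhat liberal with few events and many terms.

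**False predictors, all candidates null.** Chance of at least one term at P < .05:

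| Candidates | Stepwise | Full model, nominal .05 | 1 − 0.95^k |
|---|---|---|---|
| 3 | 12-19% | 16% | 14% |
| 5 | 22-28% | 24-27% | 23% |
| 8 | 35-46% | 38-41% | 34% |
| 10 | 45-56% | 48-54% | 40% |

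The ranges span 25 to 70 events. The stepwise and full-model columns agree within simulation error, and the number of events moves them little: at 10 candidates, about 52% with 25 events and 47% with 63 or 70.

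**The case against.** The strongest reply is that this is an ordinary exploratory method, outside the listed endpoints and outside the sample size, and that the .05 threshold is per test with no promise of control across factors. That stands, and it limits the weight of the point. It does not rescue the intervals, which would be printed as 95% intervals and are not.

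It is also fair that coverage depends on assumed candidate numbers and an assumed true effect. Even so, the shortfall is clear with only 5 candidates. The low event count rests on 51% resected. At 88.9% there would be about 45 deaths, but coverage there is still only 60-73%.

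A reader might infer more than the document supports:
- *A false predictor is about as likely as not, because of stepwise selection.* That needs about 8 to 10 null candidates. The article gives no number, and may properly leave the list to the full protocol. Nor is elimination the cause, since a full model read at the same threshold has the same rate.
- *The entry threshold is meaningless.* A backward stepwise procedure can let removed terms re-enter, so the threshold may have a role. Re-entry was not simulated.
- *The predictors will steer later treatment selection.* Nothing in the article says so.

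**Conclusion.** The point holds for estimation. Under the stated rule, nominal 95% intervals of retained predictors would cover about 60-75% (89-100 patients) or 50-65% (about 50 resected), and a hazard ratio of 1.3 would typically be reported as 1.4-1.7. These figures rest on 5 or 10 candidates, one true effect of 1.3, exponential survival and no re-entry. The direction follows from the rule itself, and the size varies with those choices.

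The false-predictor rate (about 12-28% with 3-5 candidates, 35-56% with 8-10) is a multiplicity matter and is not evidence against stepwise selection as such. The primary endpoint and the sample size are untouched. The change should be made before analysis, but it is not critical to the trial's main conclusion.

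**What to change.** In the Survival analysis section, replace the stepwise procedure and both thresholds with one Cox model on a short list of baseline factors fixed before analysis, all kept in the model. Suitable factors are already recorded for eligibility or at diagnosis: age, ECOG status, tumour size, venous versus arterial involvement, and baseline Ca 19.9.

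- Allow about 10 events per parameter. In the whole cohort 63/10 permits about six, so these five fit if each uses one parameter.
- In the resected subset, 25/10 to 45/10 permits two to four. Use fewer factors there or a penalised fit, and check that the named software offers one.
- Report every hazard ratio with its 95% interval, significant or not.
- Label the analysis hypothesis-generating and claim no 5% error control across factors. This label is needed because a five-factor model read at nominal .05 still has a 24-27% chance of at least one false predictor. If control is wanted, testing each factor at .05/k brings this to 5-7% for 3 to 5 factors.

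The cost is wording only, with no new data or patients. The downside is that fewer candidate factors are screened.

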### Safety assessment

#### Adverse event reporting

The descriptions and grading scales found in the revised NCI Common Terminology Criteria for Adverse Events (CTCAE) version 4.0 [27] will be utilized for adverse event reporting.

#### Expected adverse event reporting

Investigators must report to the PI and Coordinating Center any adverse event (AE) that occurs after the initial study treatment, during treatment, or post treatment, within 3 years of follow-up on the SAE form. This reporting requirement applies to any medical equivalent to:
an unexpected grade 2 or 3 event* with a possible, probable or definite attributionany grade 4 event, andgrade 5 (death) regardless of attribution

*Grade 2 and Grade 3 laboratory abnormalities that are considered by the investigator to be.

clinically insignificant and do not require therapy, or adjustment in prior therapy, do not need to.

be reported.

#### Routine adverse event reporting

All adverse events, whether reported by the participant, discovered during questioning, directly observed, or detected by physical examination, laboratory test or other means, must be reported in routine study data submissions to the Overall PI on the toxicity case report forms. Adverse events reported through expedited processes (e.g., reported to the IRB) must also be reported in routine study data submissions.

### Data collection and ethical considerations

The trial will be conducted according to the principles of the Declaration of Helsinki (64th version, October 2013) and in accordance with the local laws and regulations. The local principal investigator is responsible for making sure that local laws and regulations are followed.

All subjects will be recruited at the outpatient clinic by one of the principal investigators. The principle investigator may be replaced by an assigned substitute, who is fully informed and aware of the study requirements and procedures, e.g. the study coordinator or local treating physician. Patients enrolled, will be coded by a numeric code (deidentified), the principal investigator and co-investigators will be the only one with access to it. The source data will be stored digitally and will be kept by the project leader for 25 years after the inclusion of the last patient. The study will be conducted in compliance with following documents: European Directive 91/507 / EEC, Decree 211/03, D.M. December 21, 2007, AIFA Determination March 20, 2008, D.L. 189 of 08/09/2012, European Directive 2011 / C172 / 01 and Decree 2016/679. The evaluation of the study is the responsibility of the Ethics Committee, and its implementation will be possible only after its approval. Any amendment to the Protocol will follow the same approval process.

## Discussion

This phase II trial will primarily investigate the outcomes of a total neoadjuvant approach combining multiagent chemotherapy (FOLFIRINOX), hypofractionated SBRT with SIB/SIP followed by surgical resection and IORT in BRPC. Patients will be screened and enrolled at the time of diagnosis at the University of Verona Hospital Trust, a national referral center for pancreatic cancer. Because most patients referred to our center live a considerable distance away, neoadjuvant FOLFIRINOX will be administered either in Verona or at local institutions operating within a regional oncologic network, according to the patient’s area of residence. Information on the ongoing treatment will be acquired from local centers by dedicated data managers. Patients will be restaged at the coordinating center, indication to surgical exploration will be based on the evaluation of RECIST response, Ca 19.9 response and performance status by a multidisciplinary panel. SBRT, surgeries and IORT will be carried out at the Verona Pancreas Institute. Preliminary institutional experience showed that hypofractionated SBRT with SIB/SIP is feasible and is not associated with toxicity/adverse events that preclude subsequent surgical resection [12]. The addition of IORT could further reduce the recurrence or progression of the disease, ultimately impacting positively on prognosis [28]. Even the safety profile of IORT seems very favorable, with only few cases of > grade 2 acute toxicities having been reported so far in the literature [18]. Finally, in previous experiences patients undergoing pancreatic resection after neoadjuvant therapy exhibited a reduced incidence of postoperative complications, including postoperative pancreatic fistula and post-pancreatectomy hemorrhage [29].

The main strength of this study is the intention-to-treat design, in such a way that cohort-level data on recurrence and survival will be available. Furthermore, secondary endpoints including completion of neoadjuvant treatment, resection rate, toxicity, and progression-free survival can be addressed. In the subset of patients undergoing resection, per-protocol analysis of disease-free and disease-specific survival will be performed. The trial is currently recruiting. Enrollment is expected to be completed within 36 months from the study kick-off.

